## Abstract

**Background:**

For most cancers, only a minority of patients have symptoms meeting the National Institute for Health and Clinical Excellence guidance for urgent referral. For gastro-oesophageal cancers, the ‘alarm’ symptoms of dysphagia and weight loss are reported by only 32 and 8 % of patients, respectively, and their presence correlates with advanced-stage disease. Electronic clinical decision-support tools that integrate with clinical computer systems have been developed for general practice, although uncertainty remains concerning their effectiveness. The objectives of this trial are to optimise the intervention and establish the acceptability of both the intervention and randomisation, confirm the suitability and selection of outcome measures, finalise the design for the phase III definitive trial, and obtain preliminary estimates of the intervention effect.

**Methods/design:**

This is a two-arm, multi-centre, cluster-randomised, controlled phase II trial design, which will extend over a 16-month period, across 60 general practices within the North East and North Cumbria and the Eastern Local Clinical Research Network areas. Practices will be randomised to receive either the intervention (the electronic clinical decision-support tool) or to act as a control (usual care). From these practices, we will recruit 3000 adults who meet the trial eligibility criteria and present to their GP with symptoms suggestive of gastro-oesophageal cancer. The main measures are the process data, which include the practitioner outcomes, service outcomes, diagnostic intervals, health economic outcomes, and patient outcomes. One-on-one interviews in a sub-sample of 30 patient-GP dyads will be undertaken to understand the impact of the use or non-use of the electronic clinical decision-support tool in the consultation. A further 10–15 GPs will be interviewed to identify and gain an understanding of the facilitators and constraints influencing implementation of the electronic clinical decision-support tool in practice.

**Discussion:**

We aim to generate new knowledge on the process measures regarding the use of electronic clinical decision-support tools in primary care in general and to inform a subsequent definitive phase III trial. Preliminary data on the impact of the support tool on resource utilisation and health care costs will also be collected.

**Trial registration:**

ISRCTN Registry, ISRCTN12595588.

## Background

For most cancers, only a minority of patients have symptoms that meet the National Institute for Health and Clinical Excellence (NICE) guidance for urgent referral [1, 2]. For gastro-oesophageal (G-O) cancers, the ‘alarm’ symptoms of dysphagia and weight loss are reported by only 32 and 8 % of patients, respectively [3], and their presence correlates with advanced-stage disease [4]. Several other symptoms predict G-O cancer but with absolute risks in the region of 1 %. Not surprisingly, therefore, delays in diagnosis may occur; 25 % of oesophageal and 36 % of gastric cancer patients visit their GPs three times or more before diagnosis [5]; only 34 and 23 %, respectively, are referred by the 2-week wait (2WW) pathway for urgent referral of patients with suspected cancer; and 22 and 33 %, respectively, present as emergencies [6].

The primary investigation for G-O cancer is gastroscopy, whether by 2WW or direct-access referral. One solution to a diagnostic delay may be to investigate more patients. General practices in the lowest tertile of the gastroscopy referral rate (6.2/1000 per annum (p.a.)) have worse outcomes (emergency admissions, 6-month mortality) than practices in the highest tertile (16.4/1000 p.a.) [7]. Patients 55 years of age and older account for 65 % of all gastroscopies, and the gastroscopy rate in this age group is 17.5/1000 p.a. [8]. Gastroscopy rates are much higher in mainland Europe [9], probably contributing to the observed better survival. However, because gastroscopy is a costly and invasive procedure, any increase in activity should target those patients most likely to benefit.

Recent studies, including those by the co-authors, have provided robust estimates of the risk of several cancers (including G-O) for the symptomatic patient in primary care [3, 10–15]. From these, risk-assessment tools (RATs) have been developed for use in general practice [16–18]. In a feasibility study, their use was associated with increases in 2WW referrals, use of investigations, and new cancer diagnoses [19]. They have now been developed in an electronic clinical decision support (eCDS) format by Macmillan Cancer Support using the BMJ-owned Informatica platform and integrated with some GP clinical computer systems.

The Macmillan eCDS tool covers six cancer sites (including G-O cancer). It utilises either of two diagnostic algorithms: the first is based on risk-assessment tools (RAT) [3], and the second, on Qcancer research [18]. Following extensive piloting, this tool was distributed as a National Awareness and Early Diagnosis Initiative (NAEDI) project to 500 practices in 15 Cancer Networks for a pilot period of 9 months), and its usability has been qualitatively evaluated in an internal report [20]. However, the evaluation of this project did not examine the impact of the eCDS in investigations, on GPs and patients in the consultation, on clinical outcomes, or on the health economics of its use.

Despite increasing promotion of the CDS for clinical practice, great uncertainty still exists about its effectiveness for potential cancer symptoms. One systematic review has identified the features critical to success of clinical decision-support interventions [21]. A second review, of computerised (eCDS) systems, found that they improved practitioner performance in 64 % of the 97 included studies [22], whereas a third review identified prompt fatigue as a strong reason for failure of the eCDS [23]. No randomised controlled trial in primary care has reported on the eCDS for cancer diagnosis.

Important, but unanswered, questions relate to the implementation and cost-effectiveness of the cancer eCDS in primary care settings, the impact on clinical outcomes, and utility over time [24]. We propose to study this using the Macmillan eCDS tool (in its RAT version) for G-O cancer diagnosis [3] as our exemplar, for the clinical reasons listed above, for its health-economic and resource implications, and because G-O cancer has been the subject of NAEDI public awareness campaigns.

## Trial objectives

The objectives of this trial are provided below:To optimise an intervention based on the use of the G-O cancer eCDS tool, establish its acceptability, and collect relevant data to inform the design of a subsequent definitive phase III trial.To obtain preliminary evidence on the effectiveness, implementation, and cost-effectiveness of the G-O cancer eCDS tool.

At the end of this phase II trial, we will have optimised the intervention and established its acceptability [25]. We will have also generated new knowledge on the process outcomes of the eCDS in primary care and its impact on resource utilisation and healthcare costs. In a subsequent phase III trial, we will examine the effect of the eCDS on G-O cancer stage at diagnosis, on surgical treatment, and on survival.

## Methods/design

### Trial design

This is a multi-site, phase II, cluster-randomised controlled trial (RCT), supported by the North Wales Organisation for Randomised Trials in Health (NWORTH Clinical Trials Unit (CTU)). Cluster randomisation is necessary because the intervention is implemented at the practice level, but some process measures and all outcomes relate to individual patients. Patients 55 years and older, presenting to their GP with symptoms associated with G-O cancer (NICE CG17, CG27, NG12), and capable of informed consent [2, 26, 27] will be recruited from general practices, initially in the North East and North Cumbria and the Eastern Local Clinical Research Networks (LCRNs).

### Ethics

Ethical approval for this study was granted on 7 November 2014 by the NRES Committee North East - Tyne & Wear South (reference number 14/NE/1179). The study will fully comply with NHS Research Governance regulation. All necessary NHS and Durham University ethical approvals have been obtained. Informed consent will be obtained from all participants. Appropriate safety procedures will be followed by the researcher(s) when interviewing participants. Should any disclosures requiring action be made, the researchers will have access to the support of the project team.

### Study setting

We will initially use two recruitment centres, in the North East and North Cumbria and in the Eastern LCRN areas to maximise population diversity with respect to socioeconomic status and to understand feasibility issues in diverse local health economies. Practices that have participated in the Macmillan Cancer Support eCDS initiative [20] and those with incompatible software will be excluded (i.e. practices without a SystmOne Clinical Computer System).

### Sample size

This phase II trial is not powered to test specific hypotheses but to provide sufficient process data and enough participants with G-O cancer to provide estimates of effect to inform a phase III trial. We will recruit 60 practices with 1:1 randomisation, allocating 30 to each of the intervention and control arms. We anticipate that 64 patients (32 in each arm) who are subsequently diagnosed with G-O cancer will participate over the 16-month recruitment period, based on the following assumptions: (1) 17 out of every 1000 people more than 55 years of age undergo diagnostic gastroscopy for new upper gastrointestinal (GI) symptoms each year [1]; (2) 2.1 % [7] to 5.5 % (Trent Cancer Registry, personal communication) of these will have G-O cancer, depending on the route of referral (we have assumed 4 %); (3) the average practice size is 6500, with 28 % of the patients being older than 55 years of age [28], which implies that 1800 patients in each practice are age 55+; (4) 80 % of those with the index symptoms will be identifiable through READ codes (our own experience); and (5) the consent rate in the study population is 80 %. To illustrate the recruitment requirements, the number of patients with a new upper GI symptom annually ranges from 28–40/1000 [29]. Thus, from 30 control practices, we expect 1292–1843 participants, 780 diagnostic gastroscopies, and 32 patients with G-O cancer.

### Inclusion criteria

To be included, patients must be 55 years of age or older and presenting to the GP with symptoms associated with G-O cancer [10, 27].

### Exclusion criteria

Patients will be excluded according to the following criteria:If they are deemed unable to provide informed consentIf the patient did not present to a GP with upper GI symptoms within the week before the search was runIf a new prescription for a relevant medication has been made for reasons other than treatment of upper GI symptomsIf the patient has had a diagnosis made or gastroscopy performed through a route that bypassed the GP.

### Practice recruitment

GP practice recruitment will be supported via the Local Clinical Research Networks (LCRNs), who will approach practices in the designated geographical regions, favouring Research Site Initiative (RSI) practices. Recruitment will focus on RSI practices because these practices have an ongoing commitment to research and, generally, have allocated research nurse time. In practices that do not have funded research nurse time, a research nurse from the LCRNs, if possible, may be funded to support the study. Representatives from the LCRNs or study team will visit all practices interested in participating and deliver a short presentation covering the background, aims, and design of the trial. Patient recruitment will take place over 16 months or until the required number of participants has been obtained; whichever is shorter.

### Practice randomisation

Practices that agree to participate will complete an initial assessment, sign a practice agreement form and will then be randomised into one of two conditions: usual diagnostic practice (control) and usual diagnostic practice plus access to the G-O Cancer electronic risk assessment tool (eRAT) (as the intervention).

Randomisation will be undertaken by the CTU via a secure, web-based, fully validated, customised system. The randomisation will be balanced using matched-pair methodology within region. Pairs of practices within a region will be presented for randomisation, which will be randomised on a 1:1 ratio. Practices are randomised in pairs to maintain allocation concealment.

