#### Data collection

Academic research staff will visit GP practices every 6 months to extract data on participating patients to minimise any loss of data resulting from patient transfer or death. Staff will also visit gastroenterology units to extract data from secondary care patient records. All participants will be followed up for 6 months. Using data extraction templates, adapted from those developed by us for previous comparable studies, we will collect the information shown in Table 2.

**Table 2 Tab2:** The type of data collection from the two care sites

Primary care data collection
Demographic data
Date of first consultation
Duration of index (first) consultation
Dates of subsequent consultations before referral
Referral in the episode of care – Y/N
Type of referral (2WW; open access gastroscopy; routine out-patient department; emergency, other)
Date of referral
Co-morbidities
RAT used - Y/N
Date used
Duration of consultation when RAT used
Final diagnosis
Secondary care data collection
Type of referral (2WW; OAG; routine OPD; emergency, other)
Diagnosis
Date of diagnosis
Stage

Practice level data on direct-to-gastroscopy referral and conversion rates will also be collected. The East Midlands Knowledge and Intelligence Team will hold cancer waiting time data at the practice level on upper gastrointestinal (GI) 2WW referrals, conversion and detection rates, and emergency presentations.

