### Data analysis

#### Statistical analysis

Patient throughput will be summarised for the 16-month recruitment period. For *each trial arm,* we will record the (1) number of eligible patients, (2) number of eligible patients approached to take part in the study, (3) number of eligible patients that consented/are recruited to the trial, and (4) number of recruited patients for whom outcome data are collected.

We will report the percentage of all eligible patients who are recruited (participation percentage) and the percentage of recruited patients for whom outcome data are collected with 95 % confidence intervals. Separate reporting of the participation percentage by the trial arm will help identify any obvious recruitment bias resulting from randomising the practices before recruiting patients to the trial. However, we consider the risk of serious recruitment bias to be low because all eligible participants from intervention or control practices will be invited to participate, and this will be done by post after the index consultation, rather than during the consultation.

General practices in the intervention and usual-care arms will be described separately with respect to region (a factor used to balance the randomisation). Participating patients will be described separately within each trial arm with respect to relevant baseline demographic characteristics, using means and standard deviations (or medians and interquartile ranges) for continuous variables and percentages for categorical variables. No formal tests of significance will be used for these descriptive analyses.

It is not a primary objective of the study to obtain definitive estimates of the intervention effect on study outcomes. However, comparisons between the intervention and control arms using the intention--treat principle will be reported as ancillary analyses. A comparison of binary outcomes will be implemented using marginal logistic regression models using generalised estimating equations (GEEs) with information sandwich (‘robust’) estimates of standard error, specifying the correlation structure as exchangeable. In the case of rare binary events, the responses will be summarised using percentages only. Comparison of time-to-event outcomes will be carried out using marginal proportional hazards models with information sandwich (‘robust’) estimates of standard error.

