Binary outcomes will be reported using a percentage for each trial arm, an odds ratio for comparing the trial arms, a 95 % confidence interval, and *p*-value. Time-to-event outcomes will be presented as the hazard ratio, confidence interval, and *p*-value. Crude estimates of intervention effect and estimates adjusted for region and practice size will be presented. The following outcomes will be compared:For all patients○ Whether the patient is referred (binary)For all referred patients○ Whether the patient is referred via the 2-week wait pathway (2WW) (binary)○ Whether patient is referred via the direct-access pathway (binary)○ Whether the referred patients were diagnosed with cancer (conversion – binary outcome)For all patients with cancer○ Whether the diagnosed patients had been referred via the 2WW/direct-access pathway (binary outcome)For patients referred via the 2-week wait○ Cancer conversion rate (binary outcome)For patients referred via the direct-access pathway○ Cancer conversion rate – (binary outcome)For patients diagnosed with cancer○ Stage at diagnosis○ Treatment with curative intent (binary outcome),○ 1-year and 3-year survival○ Diagnostic interval (time from symptomatic presentation to cancer diagnosis)

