## Discussion

The objectives of this trial are to optimise the intervention and establish the acceptability of both the intervention and randomisation, confirm the suitability and selection of outcome measures, finalise the design for the phase III definitive trial, and obtain preliminary estimates of the intervention effect. These outputs need to be obtained before conducting a definitive trial, which would determine the effect on patient outcomes (the stage at diagnosis, treatment with curative intent, 1-year and 3-year survival, and diagnostic interval), resulting from the introduction of the eCDS into general practice for suspected G-O cancer.

We will use the Medical Research Council framework for the design and evaluation of complex interventions [25, 33, 34]. We are conducting a phase II, exploratory, cluster-randomised controlled trial to evaluate an eCDS tool for suspected G-O cancer (the e-RAT [3]).

The use of the eCDS in intervention practices may result in a change in practice activity levels for gastroscopy. The direction of effect is uncertain, since any increase in activity may be offset by fewer unnecessary referrals. An absolute 10 % increase in gastroscopies in the intervention arm would constitute an additional 32 gastroscopies in each network area.

Public awareness campaigns for G-O cancer have been run as part of the Be Clear on Cancer campaign and resulted in an increase in GP consultations and referrals. If such a campaign runs in either or both of the two recruitment areas during the recruitment period, we will monitor and describe it.

New NICE guidance on the investigation of possible cancer was published in July 2015 after the study was designed and ethical approval was obtained but before recruitment had begun. The NICE guidance was based in part upon the research underpinning the eRAT, so control practices (if they fully adhere to the new guidance) may offer investigative practice closer in nature to the intervention practices than was expected at the time of the trial design. Adoption of the NICE guidelines (NG12) may also occur at different rates between the different clinical commissioning groups.

This is one of the first trials of eCDS for the early diagnosis of symptomatic cancer and will be completed in 2018.

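### The adjusted comparison of referral omits each practice's pre-trial referral rate, although the Background cites a 2.65-fold spread in practice gastroscopy rates; the cost is precision, not validity

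*Protocol article*

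**What the plan says.** Under Practice randomisation, the protocol article states: "The randomisation will be balanced using matched-pair methodology within region". It continues: "Pairs of practices within a region will be presented for randomisation, which will be randomised on a 1:1 ratio". The reason it gives for pairing is concealment, not prognostic similarity: "Practices are randomised in pairs to maintain allocation concealment".

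Under Statistical analysis, practices are to be "described separately with respect to region (a factor used to balance the randomisation"). Binary outcomes are compared by marginal logistic GEE models with an exchangeable correlation and robust standard errors. Besides crude results, "estimates adjusted for region and practice size will be presented". The first outcome listed, for all patients, is whether the patient is referred. The comparisons between arms are called ancillary.

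The Background gives practice gastroscopy rates of 6.2 per 1000 a year in the lowest tertile and 16.4 in the highest, and links the low rate to worse outcomes. Under Data collection, "Practice level data on direct-to-gastroscopy referral and conversion rates will also be collected"; upper GI 2WW referrals at practice level will also be held. No period is given for either.

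**The concern.** In a cluster trial with 30 practices per arm, the precision of a between-arm comparison depends heavily on how much practices differ before the intervention starts. The article itself cites a large spread in the practice behaviour closest to its first listed outcome. Neither the named balancing factor nor the two named covariates measures that behaviour directly: region is coarse, and practice size is not a referral rate.

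At stake are the preliminary effect estimates. The Sample size section says the trial should supply estimates of effect for phase III, and the Process and outcome measures section takes the control-arm referral proportion as an input to the phase III power calculation. A difference in habitual referral between the two sets of practices feeds into the effect estimate, and a baseline covariate would remove part of it.

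**Working it through.** **Plan's own figures.** The article gives no between-practice variance and no figure for chance imbalance, so there is none to reproduce on this exact point. Its expected yield from 30 control practices does reproduce, which confirms the cluster count used below:
- Gastroscopies: 30 × 1800 × 0.017 × 16/12 × 0.80 × 0.80 = 783 (stated 780).
- Cancers: 783 × 0.04 = 31.3 (stated 32).
- Participants, using 28 and 40 per 1000 in place of 17: 1290 to 1843 (stated 1292 to 1843).

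**Inputs.**
- Tertile rates 6.2 and 16.4 per 1000 a year (Background). Ratio 16.4/6.2 = 2.65.
- 30 practices per arm (Sample size).
- Assumption A: the two rates are tertile means, and trial practices vary as those practices did.
- Assumption B: the practice's gastroscopy habit carries over in proportion to referral of recruited patients.
- Assumption C: region and practice size explain none of this spread.

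**Normal model.**
1. The mean of the top third of a standard normal is 1.091, so the tertile means lie 2 × 1.091 = 2.18 SD apart.
2. SD between practices = (16.4 − 6.2)/2.18 = 4.67 per 1000. Midpoint = (6.2 + 16.4)/2 = 11.3 per 1000.
3. SE of the difference between arms = 4.67 × √(2/30) = 1.21 per 1000, or 1.21/11.3 = 10.7 % of the mean.
4. 95 % range = ±1.96 × 1.21 = ±2.4 per 1000, or ±21 % of the mean.
5. P(difference above 10 % either way) = 2 × [1 − Φ(10/10.7)] ≈ 0.35.

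**Lognormal model, as a check.** The SD on the log scale that gives a ratio of 2.65 between tertile means is about 0.444. The SE of the log ratio between arms is 0.444 × √(2/30) = 0.115, and the 95 % range of the ratio is 0.80 to 1.25. P(ratio beyond 1.10 or its reciprocal) ≈ 0.41, and beyond 1.20 about 0.11. The two models agree.

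**Effect of adjustment.** With correlation r between the pre-trial and in-trial practice rates, the SE is multiplied by √(1 − r²). The documents give no r.

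| Assumed r | Multiplier | 95 % range |
|---|---|---|
| no adjustment | 1.0 | ±21 % |
| 0.6 | 0.8 | ±17 % |
| 0.8 | 0.6 | ±13 % |

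**If the spread is smaller.** Were the SD half as large (2.34 per 1000), the SE would be 2.34 × √(2/30) = 0.60 per 1000, or 5.3 % of the mean. The range would be ±10 %, with about a 6 % chance of exceeding 10 % under the normal model (10 % under the lognormal).

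**The case against.** The case against has force on several points.

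- A reader might infer that pairs are matched on region and nothing else. The article does not say so. It calls region a factor, not the only one. Practices also complete an initial assessment before randomisation whose content is not described, and a condensed article may leave matching variables to the full protocol. What stands is that region is the only factor named.
- A reader might also infer that the plan demonstrates uneven guideline uptake, and that this adds to imbalance. The Discussion says only: "Adoption of the NICE guidelines (NG12) may also occur at different rates between the different clinical commissioning groups". That is a caveat without data, so no weight is put on it here.
- The tertile rates are for practices in general and are population rates. They depend partly on age structure and on how often patients consult, and restricting to symptomatic patients aged 55 or over removes much of that. Trial practices are also selected, with SystmOne required and research-active sites favoured. The spread in the trial's own referral outcome may therefore be smaller, and the ±21 % is conditional on its not being so.
- Choosing covariates can be left to the analysis plan, which the steering committee is to approve. Here, however, the article already names the adjustment set, so this is a comment on a stated method and not on missing detail.
- The trial is unpowered, the comparisons are ancillary, and randomisation with robust standard errors is valid. All of this is right, and it limits the weight of the point. It does not remove the point, because preliminary effect estimates are a stated objective and a covariate can sharpen them.

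**Conclusion.** The point holds as one about efficiency. The stated adjustment for region and practice size omits a practice-level predictor that the article's own Background suggests is important. Under assumptions A to C, the chance difference between arms has a 95 % range of about ±21 % of the mean rate and exceeds 10 % with probability of about 35 to 41 %. If trial practices vary less, both figures fall, to about ±10 % and 6 to 10 % at half the spread.

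Two stronger conclusions are not supported. One is that the imbalance will outweigh the 10 % rise in gastroscopies mentioned in the Discussion. On these figures most allocations give a smaller difference than that, and the 10 % is a workload illustration, not a target effect. The other is that the estimates would be biased. Allocation is random, and between-practice variation is already carried into the confidence intervals through the robust standard errors. What is lost is precision in ancillary estimates.

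**What to change.** For the outcome of whether the patient is referred, add each practice's pre-randomisation referral rate (direct-access gastroscopy and upper GI 2WW) to region and practice size in the adjusted GEE model. Do the same for the referral-route outcomes where event numbers allow. Tabulate this rate by arm alongside region. Obtain it by asking the practice-level sources already named under Data collection for the 12 months before each practice's randomisation. This can cover practices that have already been randomised.

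The cost is one further data period and one further covariate. Because the article states no period for these data, their availability before randomisation must be confirmed first. The gain depends on the before-after correlation, which is unknown.

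Leave the pairing rule unchanged. Site recruitment is under way, and altering the rule now would put two allocation schemes in one trial and could delay practices waiting for a partner.
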